#### Interim analysis plan

A single interim data analysis of Specific Aim 1 (ASAP vs DEUCC) for only the primary outcome, WMFT time, will be performed when approximately 33% of the participants have completed the 1-year evaluation. The O’Brien-Fleming group sequential method [92] will be used with the significance level defined as 0.005 at the interim analysis to maintain the overall type I error of 0.05. The advantage of the O’Brien Fleming method is: 1) it is conservative for significance at the interim analysis point, and 2) it maintains the conventional p-value in the final analysis. Group assignment will remain blinded with codes X and Y representing either ASAP or DEUCC groups to avoid revealing treatment assignment. Only the primary outcome for the primary aim (log WMFT mean time) will be analyzed as described above. If the test of success rate in WMFT time at the interim analysis point reaches a p-value less than these critical p-values, the DSMB will decide whether analysis of secondary outcomes is necessary to provide additional support of the results. If deemed necessary by the DSMB, conditional power will be computed to make a reassessment of the power at the end of the trial.

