**Methods/design:**

Following baseline assessment, participants are randomized by site, stratified for stroke duration and motor severity. 360 adults will be randomized, 14 to 106 days following ischemic or hemorrhagic stroke onset, with mild to moderate upper extremity impairment, recruited at sites in Atlanta, Los Angeles and Washington, D.C. The Wolf Motor Function Test (WMFT) time score is the primary outcome at 1 year post-randomization. The Stroke Impact Scale (SIS) hand domain is a secondary outcome measure.

The design includes concealed allocation during recruitment, screening and baseline, blinded outcome assessment and intention to treat analyses. Our primary hypothesis is that the improvement in log-transformed WMFT time will be greater for the ASAP than the DEUCC group. This pre-planned hypothesis will be tested at a significance level of 0.05.

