### Statistical analysis

#### Sample size and participant accrual

Sample size estimates were computed for the primary *a priori* aim of detecting a clinically relevant difference in log-transformed WMFT time score between ASAP and DEUCC at 1 year follow up with α = 0.05. With the proposed total sample of 360, we would have sufficient power to detect a moderate difference in treatment effect of Δ = 0.40 for an attrition rate of 17%, and Δ = 0.42 for an attrition rate of 25% using a two-group 2-sided t-test with a type I error of 0.05 and 80% power. The EXCITE trial showed treatment effect sizes of 0.50 and 0.63 for the high and low functioning groups, respectively. For the small sample phase II VECTORS study, a similar analysis showed a treatment effect size of 0.20. Given the outpatient timing of ICARE, a less dynamic period of change than VECTORS, we expect to have sufficient power to detect the effect size in log WMFT time score. We also should have sufficient power to detect a difference in the proportion of participants who change ≥ 25 points on the normalized SIS at 1 year using a χ^2^ statistic. The minimal success rate difference that can be detected with 80% power ranges from 13.5-20% (with 17% attrition) to 14.0-21% (with 25% attrition); the variation in the estimates reflects potential variation in improvement in the DEUCC group. To achieve this recruitment goal (N = 360) in 40 months, each of the three centers aims to randomize 3 participants per month.

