#### Analysis plan

This trial addresses two different questions separated by primary aim and secondary aim: 1) Is ASAP superior to DEUCC (primary aim)?, and 2) Is ASAP or DEUCC superior to UCC, (secondary aim) For all analyses, assumptions required for the data distribution (e.g., normal distribution) will be assessed. Any transformations of data or alternative methods necessary to analyze the data will be determined by examining the structure of the data. All analyses will be performed in accord with the intent-to-treat (ITT) principle (e.g., group status is determined by randomization at baseline). A p-value < 0.05 will be used to indicate statistical significance for all analyses.

The primary aim analyses will compare the ASAP and DEUCC group change in log WMFT time score and success rate from the SIS hand domain and the full SIS. For the primary hypothesis, change in WMFT time score at 1 year, an independent sample t-test will be used to compare the mean change in log-transformed WMFT time score, and analysis of covariance (ANCOVA) will be used to adjust for *a priori* covariates (site, initial motor impairment, stroke duration to randomization, baseline log time score) and any baseline variables that were imbalanced between ASAP and DEUCC. For missing data from loss to follow-up or missed evaluations at 12-months, multiple imputation using all available evaluation data will be utilized. Adjusted least-square means and the associated 95% confidence interval will be presented as well as p-value, and effect sizes will be computed to aid in interpretation of results.

For the secondary hypothesis, the success rate of the SIS hand domain will be calculated as the percent of subjects in the ASAP and DEUCC groups that achieved at least a 25-point increase in normalized SIS hand function at 1 year post randomization compared to baseline. Logistic regression will be used to compare these rates between groups, while adjusting for covariates. Since there are no prior data or biological evidence suggesting that ASAP will have a differential effect on one subgroup compared to DEUCC in the targeted population, we are not planning any *a priori* interactions between treatment and any of the covariates in the main analysis. However, we will perform exploratory data analysis to examine these possible interactions and generate hypotheses for future studies.

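### An interim level of 0.005 at one-third information is not the O'Brien-Fleming boundary, and with 0.05 kept at the end the overall type I error is about 5.3%, not 5%

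*Protocol article*

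**What the plan says.** The protocol article, section *Interim analysis plan*, schedules "A single interim data analysis of Specific Aim 1 (ASAP vs DEUCC) for only the primary outcome, WMFT time". The look "will be performed when approximately 33% of the participants have completed the 1-year evaluation". The O'Brien-Fleming group sequential method "will be used with the significance level defined as 0.005 at the interim analysis to maintain the overall type I error of 0.05". One advantage claimed for the method is that "it maintains the conventional p-value in the final analysis".

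The final level appears in two other places:
- *Analysis plan*: "A p-value < 0.05 will be used to indicate statistical significance for all analyses".
- *Abstract*, Methods/design, on the primary hypothesis: "This pre-planned hypothesis will be tested at a significance level of 0.05".

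*Sample size and participant accrual* makes the test two-sided: power is computed "using a two-group 2-sided t-test with a type I error of 0.05 and 80% power". The article gives no reduced level for the final primary test. *Current study status* reports that the interim analysis was completed in November 2011 and that recruitment continued.

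**The concern.** O'Brien-Fleming allows the conventional level to be nearly kept at the end because it spends almost nothing at an early look. An interim level of 0.005 is the familiar two-look O'Brien-Fleming value for a look halfway through. At one third of the information the method gives a much smaller level. If 0.005 is applied that early and the final test is left at 0.05, more than 0.05 is spent in total.

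At stake is the error rate claimed for the single confirmatory test of a phase III trial. A final p just under 0.05 would be called significant under a rule that does not control the error at 5%. Because the look has been taken, the interim level can no longer be chosen; only the final level remains open.

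**Working it through.** **Inputs**
- Two looks in total, one interim and one final (*Interim analysis plan*).
- Interim two-sided level 0.005, so c1 = 2.807 (*Interim analysis plan*).
- Final two-sided level 0.05, so c2 = 1.960 (*Abstract*, *Analysis plan*; two-sided from *Sample size and participant accrual*).
- Information fraction t of about 1/3 (*Interim analysis plan*).

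**Step 1: overall error of the rule as written.** Under the null hypothesis the interim and final statistics Z1 and Z2 are bivariate normal with correlation √t = √(1/3) = 0.577. The overall error is

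α = 1 − P(|Z1| < c1 and |Z2| < c2) = P(|Z1| > c1) + P(|Z2| > c2) − P(both exceeded).

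At t = 1/3: 0.005 + 0.050 − 0.0021 = **0.0529**. A simulation of 8 million null trials also gave 0.0529. The article's figure of 0.05 is not reproduced.

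**Step 2: the O'Brien-Fleming boundary at the stated timing.** The two-look boundary is c/√t at the interim and c at the end, with c solved so that α = 0.05. At t = 1/3, c = 1.962:
- interim z = 1.962/0.577 = 3.40, p = 0.00068;
- final p = 0.0497.

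The Lan-DeMets O'Brien-Fleming-type spending function gives nearly the same pair, 0.00069 and 0.0497. At t = 1/3 the stated 0.005 is about seven times the O'Brien-Fleming interim level (0.005/0.00068 = 7.4).

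**Step 3: where 0.005 does belong.** The O'Brien-Fleming interim level equals 0.005 at t of about 0.50. At t = 0.50 the pair is 0.0052 and 0.0480, so that design does not keep 0.05 at the end either.

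**Step 4: the final level that restores 0.05 if 0.005 was used.** Holding c1 = 2.807 and solving for c2 at t = 1/3 gives c2 = 1.986, a two-sided final level of **0.0470**.

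**Step 5: sensitivity to timing.** The article gives a proportion of participants, not an information fraction. If 33% means 33% of all randomised and 17% are eventually lost, t is about 0.33/0.83 = 0.40.

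| t | Overall α with 0.005 then 0.05 | Final level needed after 0.005 | O'Brien-Fleming interim | O'Brien-Fleming final |
|---|---|---|---|---|
| 0.25 | 0.0534 | 0.0465 | 0.0001 | 0.0500 |
| 0.33 | 0.0529 | 0.0470 | 0.0006 | 0.0497 |
| 1/3 | 0.0529 | 0.0470 | 0.0007 | 0.0497 |
| 0.40 | 0.0525 | 0.0474 | 0.0019 | 0.0492 |
| 0.50 | 0.0519 | 0.0481 | 0.0052 | 0.0480 |

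**Step 6: one-sided readings.** At t = 1/3, one-sided levels of 0.005 then 0.05 give 0.0524 against 0.05, and 0.005 then 0.025 give 0.0282 against 0.025. Neither rescues the statement.

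**Step 7: power.** With 120 × 0.83 = 99.6 per arm and a difference of 0.40 SD, a two-sided t-test has 80.2% power at 0.05, which agrees with the article's 80%, and 79.5% at 0.047. The loss is 0.7 percentage points.

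**The case against.** The arithmetic is not in dispute; the case against is about weight and certainty.

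- *The effect is very small.* This stands. The excess is 0.29 percentage points at t = 1/3 and 0.25 at t = 0.40.
- *Crossing 0.005 is not stated to be a rejection.* The section only has the DSMB decide whether to look at secondary outcomes. If the interim could never support an efficacy claim, nothing would be inflated. This stands as a condition on the 5.3%. But the article presents 0.005 as the means of holding the overall error, which makes sense only if crossing it counts.
- *The sevenfold ratio depends on timing.* This stands. At t = 0.40 the ratio is 0.005/0.0019, about 2.7. The overall error still exceeds 0.05 there.
- *A condensed article may have dropped a final boundary.* The general 0.05 rule is overridden at once by 0.025 for the comparisons with UCC, and the interim text mentions critical values in the plural while giving one. This does not remove the point: the final level is stated as conventional, and the Abstract fixes 0.05 for the primary hypothesis.
- *The claim about the final level is the usual loose description of O'Brien-Fleming.* That is fair for a true bound: about 0.0007 at the interim followed by 0.05 gives 0.0503. It is not fair with 0.005 printed beside it.

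**Conclusion.** The concern holds. The named method, the 0.005 level at about one-third information and an unreduced final 0.05 do not together give an overall type I error of 0.05. The rule as written gives 0.0529, with a range of 0.0534 to 0.0519 for information fractions from 0.25 to 0.50. This rests on two-sided tests, one interim look, and crossing 0.005 being treated as rejection. The practical reach is narrow: at t = 1/3 only a final p between about 0.047 and 0.050 would be classified differently. It is still an incorrect statement about the error rate of the primary test, and it should be corrected before the final data are seen.

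**What to change.** 1. State the bound the DSMB actually applied in November 2011 and the information fraction then available for ASAP against DEUCC.
2. Set the final two-sided level for the primary WMFT comparison to match. If 0.005 was used, this is about 0.047 at one-third information (0.0465 to 0.0474 for fractions of 0.25 to 0.40). If a true O'Brien-Fleming bound of about 0.0007 was used, it is 0.0497. Recompute either from the actual fraction.
3. Remove the claim that the conventional level is kept, exempt the primary test from the general 0.05 rule in *Analysis plan*, and align the Abstract.
4. Say whether crossing the interim bound counts as rejecting the null hypothesis.
5. As a minor tidy-up in the same section, the sentence on crossing the bound refers to a success rate for WMFT time. The primary test concerns mean change in log WMFT time, and the wording should say so.

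The cost is wording in the protocol and the matching SAP text, plus about 0.7 percentage points of power if the final level becomes 0.047. No change to sample size or conduct is needed.

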#### Missing data

The DMAC conducts weekly checks for all expected measurements in the database. Missing data must be identified by the cause of missing data, (e.g. participant not able to complete the measurement or evaluator error, forgot to record the data). Detailed reasons for missing data are recorded in a comment box under each measurement. This missing data form/point control procedure will enable future analysis for missing data patterns (e.g., systematic or random), and thus, support decision making for final data analysis.

### Adverse event monitoring and reporting

Adverse events (AE) are monitored closely and supported by the ICARE database that sends auto-alerts to team members, the NINDS clinical trial liaison to the DSMB and the Medical Safety Monitor (MSM). AEs include new events not present prior to enrollment in the study or events that were present during the pre-enrollment period but have increased in severity. All adverse events are reported in terms of three factors: 1) Serious or Non-serious, 2) Expected or Unexpected, 3) Related or Unrelated. These discrete categories and each characteristic of the event are evaluated independently of the others. An AE is considered serious (SAE) if it involves death, a life-threatening event, inpatient hospitalization, or persistent and/or significant disability/incapacity that lasts more than 48 hours, limits activities of daily living, and (in the opinion of the investigators) represents significant hazard or potential serious harm to the participant or others. Non-serious events are minor events that do not seriously limit a participant’s activities of daily living or present a potential risk to the participant or others. Expected serious events include: recurrent stroke or TIA; myocardial infarction or acute coronary syndrome; new onset of cardiac arrhythmia; fracture; pulmonary embolism; inpatient hospitalization or ER visit greater than 23 hours; and death. Expected non-serious events include: fall with no fracture; dyspnea; open sore or cuts; muscle soreness or pain that persists for more than 48 hours; shoulder pain that limits study participation; excessive blood pressure responses that require treatment discontinuation for the day; dizziness/fainting; deep vein thrombosis, without pulmonary embolus, and depression requiring mental health intervention. A related adverse event reflects a realistic chance of a causal relationship between participation in the study and the adverse event as suggested by an event that follows within a reasonable time after research procedures (i.e., 24 hours), follows a pattern consistent with study procedures, improves when study procedures have stopped and/or reappears when the procedures in question are repeated. An adverse event that does not reflect a realistic chance of a causal relationship between participation in the study and the adverse event, as described above for a related adverse event, is an unrelated adverse event.

#### Adverse events reporting procedures

The adverse event reporting system was developed with NINDS guidance, and has a pre-planned, automatic work-flow that triggers instant electronic communication. A site team member completes the online “Adverse Event Initial Report Form” within 24 hours of knowledge of an event and in compliance with all local IRB reporting procedures. This initiates the report process. The initial report is instantly added to the ICARE database and triggers an immediate, automatic notification to the study PIs, project manager, originating site’s physician investigator and clinical site coordinator, and DMAC members. The site physician investigator is responsible to obtain all necessary facts to verify and adequately describe the event, determine seriousness, determine the appropriate course of action and report these items via the ICARE “Adverse Event Confirmation Form” to the database within 72 hours after the initial report submission. If the AE is confirmed as serious, an immediate, automatically triggered email notification with a narrative of the SAE is sent to the study PI’s, project manager, originating site’s physician investigator and clinical site coordinator, MSM and the DSMB liaison. The MSM will review the SAE narrative and adjudicate study-relatedness and expectedness within 5 days (120 hours) of the automated email notification of an SAE. If data are not entered within the first 96 hours, an automated courtesy reminder is sent to the MSM. A detailed AE report is generated weekly and available to all study personnel. An AE summary report is generated and reviewed quarterly by the Data Safety and Monitoring Board (DSMB) and the USC IRB. Each site reports to its respective IRB in accordance with its policies and procedures. All AE reports, and amendments to them, are recorded and monitored by the DMAC.

### Data management and quality

#### Data management

The DMAC consists of the director, who is the unblinded statistician and who is responsible for managing the DMAC and acting as liaison to the DSMB for data-related matters, including preparation of reports and analyses (interim and primary outcomes). The other DMAC members are staff from USC’s Statistical Consultation and Research Center and include a co-director in charge of database development and management, a programmer, data manager and two research assistants. Additionally, a blinded statistician serves on the executive committee and is able to answer statistical questions that arise without danger of breaking the blind of the study.

#### Quality control procedures

Microsoft® SQL Server 2000 Edition is utilized for the secure database. This database is configured to utilize transaction logging for auditing and recovery purposes. All data entry/retrieval travels over the Hypertext Transfer Protocol Secure (HTTPS) layer. Backups are conducted daily, weekly, monthly and quarterly. The backup files are stored in a backup server at a secure separate location. The WMFT video files are stored in a multimedia server and streamed to the data entry system with the corresponding accession number, which provides blinding to site and evaluation time point.

Users are issued individual usernames and passwords to gain access to the secure web-based data entry system. Since ICARE is a multisite study, each site has access only to its site- specific data records. Within each site, only designated personnel can enter and modify data. The blinded evaluators are prohibited from accessing any treatment related information in the database, including randomization assignment.

All clinical report forms (CRF) are barcoded to prevent ID error. Sites are required to scan and submit the original CRFs for all key outcome measurements to the DMAC for data entry quality checking. Quarterly, the DMAC performs data quality checking (QC) on 100% of primary outcome data (WMFT and SIS).

### Study organization and management

ICARE is conducted by an experienced multidisciplinary research team, and is managed through a series of committees. This trial uses a multiple-PI management plan with the following designations: PI#1 is [name], PT, FAPTA, PI#2 is [name], and PI#3 is [name], PT, FAPTA. PI#1 chairs the executive committee (EC), the small study leadership group that guides ICARE implementation and operations. This committee is composed of the PIs, study project manager (PM), blinded statistician and DMAC consultant, and NINDS scientific program director. It meets weekly by conference call. The EC is responsible for the general design and conduct of the study, protection of human research subjects, review of study progress and data collection, changes in study procedures, allocation of resources, and communication with the DSMB and NINDS. All dissemination ideas are vetted through the Executive Committee. When necessary the EC invites the DMAC Director, to participate in the meeting especially for preparation and discussion of DSMB reports. PI#1, 2 and 3 lead implementation of the scientific agenda and specific aims and ensure that systems are in place to guarantee responsible management of the RCT.

PI#1 serves as the primary contact PI, assumes fiscal and administrative responsibility for the trial and plays a lead role in the training and standardization of the ASAP therapists, including development of multi-media training tools. The DMAC, in consultation with PI#1 and the PM, develop and provide all reports to the DMSB and the NIH in accord with a pre-established time line for reporting.

PI#2 is responsible for all medical and neurologic issues that arise during participant screening, therapy, and follow-up. As study medical director, he is responsible for identification of stroke diagnosis and characterization and inclusion/exclusion criteria related to medical and diagnostic features of study participants. This responsibility includes review of brain images and response to diagnostic queries, review of adverse events and communication with the DSMB liaison when appropriate.

PI#2 and 3 are responsible for managing their subcontract and providing leadership at their respective Center including all clinical affiliates (PI#2 NRH; PI#3 Emory) to assure that each center investigative and clinical team implement the trial in accord with all policies and procedures detailed in the MOP. Additional leadership at each geographic center is provided by a designated center coordinator. Each site is led by a Clinical Site Coordinator (CSC) and Site Physician Investigator (SPI). For each of the roles of CSC, SPI, intervention therapist and blinded evaluator, there are trained, standardized back-up personnel. An experienced clinician oversees training and certification for the WMFT, with consultation from the tool’s developer (PI#3) and the PM. All PIs, the PM and DMAC Director share in monitoring study progress, including: recruitment, adherence, retention, safety and missing data. The Executive Committee guides the management of issues identified study-wide; whereas PI#1, the PM and, when necessary, the DMAC Director, manage site-specific issues. Both groups collaborate with the site teams to implement solutions and monitor effectiveness. PI#1, the PM and DMAC Director visit each site annually to monitor data quality, process and compliance and consult regarding site-specific issues. PI#1 and the PM coordinate with the DMAC on website and informatics work, to issue weekly progress reports to the investigative and clinical teams, and to maintain and update the MOP and CRFs as needed.

The Data Safety and Monitoring Board (DSMB) is appointed by the NINDS to ensure highest quality and ethical study execution and consists of a stroke neurologist, a physical therapist, a rehabilitation neurologist, a biostatistician, and an NINDS DSMB liaison. The DSMB evaluates a full study report, prepared by the DMAC Director and Project Manager, biannually. This report provides a summary of study activities, issues and progress since the last report in narrative form followed by data tables and figures, which include grouped data sets, blinded for treatment allocation. As an appendix to the report, each site prepares a site-specific narrative including proactive strategies for any areas of concern. Both the main report and the site-specific reports address the primary issues of: participant accrual, execution of intervention adherence (ASAP & DEUCC only), retention, safety and data quality, including missing data, protocol adherence, and safety. An abbreviated report is evaluated by the DSMB during the interceding quarters. The DSMB monitors serious adverse events and reviews cumulative adverse event data quarterly to ensure study safety. These data are also grouped, but blinded for treatment allocation. The DMAC Director prepares unblinded reports and analyses if requested by the DSMB. The DSMB meets biannually with the Executive Committee, DMAC Director, and MSM, alternating between tele-conference and in person meetings per annum. Additional meetings may be scheduled at the discretion of the DSMB or NINDS.

An independent Medical Safety Monitor (MSM) is chosen by the NINDS staff and the Executive Committee. This rehabilitation physician is responsible for timely review and adjudication of all serious adverse events and for reviewing summary reports of all adverse events on a regular basis. The MSM attends the annual DSMB meetings as well as the quarterly phone meetings.

The Clinical Site Coordinator (CSC) Committee consists of the Project Manager, and seven Clinical Site Coordinators; a DMAC member, PI#1 and other study personnel join as needed. This committee is responsible for collaborative training and problem-solving; recruitment, protocol implementation; data entry; resolution of site differences and assurance of trial consistency. This committee meets twice monthly.

The Clinical Research Committee is comprised of PI’s #1, 2 and 3, the PM, the three Clinical Center Coordinators (CCC), the DMAC Director and the psychosocial consultant. It meets monthly and is responsible for strategic planning, protocol development and implementation, CRF development and identification and development of secondary research questions.

The Physician Investigator Committee consists of the seven physician investigators across the clinical sites, the CCC, the PM, and PI#1. This group addresses relevant medical issues, assists in study recruitment, develops strategies to enhance recruitment, and facilitates acquisition of neuroimaging studies for secondary analyses. This committee will generate topics for secondary publications relevant to ICARE and the medical management of sub-acute stroke.

A Blinded Evaluator Committee consists of all blinded evaluators across the three centers, the CCC, PM and the WMFT reviewer. The BE committee focuses on standardization and execution of measurement, assurance of data completeness, participant safety, and prevention and documentation of unblinding.

The Publications Committee is comprised of the three PIs and the DMAC Director. It will establish a policy and oversee study publications to ensure that they are ethical and of high scientific quality. The committee will mediate when there is disagreement about an issue related to the form or scope of the publication and related issues including authorship. While generally not responsible for decisions regarding content, the committee may intervene in cases where a manuscript may include claims or interpretations that are not supported by the data. All publications emergent from the ICARE database will be vetted through the publications committee.

